### Intervention

The intervention being evaluated is a structured cell phone initiative to improve communications between healthcare providers and patients. The intervention protocol was conceived in 2005 by several brainstorming meetings between health care provider staff at the clinics, and ultimately incorporated feedback from pilot patients from a survey and from small group sessions[3].

Every week, on Monday mornings, the site-clinician (typically a nurse or clinical officer) sends a text message (SMS) to all subjects in the intervention arm to remind them about their support and enquire into how they are doing. Typically, a slogan is used such as "Mambo?" which is Kiswahili for "How are you?", but similar slogans in other local languages can also be used at the clinicians' discretion. To simplify their work, the clinicians use the 'send to many' function on their cell phone for mass/group messaging. Intervention subjects are instructed to respond within 48 hours either that they are doing well ("Sawa") or that they have a problem ("Shida") and request assistance. Sending an SMS is inexpensive (less than $0.05); however, in some circumstances where network credit is not available or was impractical, the patients can use the free 'flashback' function to trigger a call from the clinician. The clinician then calls to follow-up and provide triage to any subjects that respond that there is a problem, or subjects who fail to respond within two days.

Clinicians are only expected to respond to text messages during regular clinic hours, but are not restricted to do so. Intervention participants are instructed that the intervention is a clinic utility and that all emergencies should be handled through their usual means such as attending the nearest hospital emergency department. All participants receive a brief training from the clinicians on use of the phone and the protocol if they were in the intervention. Use of any of the cell phone network providers is allowed. Receiving SMS text messages or voice calls in Kenya is free on all networks.

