#### Secondary objectives

We will also test the cell phone intervention (SMS) ability to improve health, quality of life, social, economic outcomes and retention in ART programs. We hypothesize that patients who receive the weekly SMS reminders (intervention) may have improved immune reconstitution (CD4 count), increased body weight, fewer opportunistic infections, fewer adverse health events, improved quality of life, delayed death, improved social factors such as disclosure of their HIV status, and improved economic indicators compared to those that do not receive the intervention (control). We also hypothesize that subjects in the intervention arm will be more frequently retained in the ART program.

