### Data collection

Data collection tools include a baseline questionnaire, follow-up questionnaire (used at 6 and 12 month visits), the SF-12 quality of life assessment adapted for local content, GPS co-ordinates of the clinics and participants homes, and a household roster of economic indicators. Questionnaires include continuous and categorical variables and Likert scales. All questionnaires were designed in English and translated to Kiswahili then back translated to verify meaning. Questionnaires are administered by clinic staff fluent in the languages of participants. In instances where study participants speak only local languages, the clinician translates questions directly. Antiretroviral adherence is assessed at each follow-up visit by inquiring about missed doses in the previous 30 days and calculating percent adherence according to pill counts. A visual analogue scale is used to confirm calculated adherence rates. A weekly study log is kept to record the weekly SMS messages and responses including details related to phone access, medication adherence and health or illness issues as they arose. Telephone communications with subjects in the control arm are also recorded in a similar study log, even though they are not sent the weekly SMS messages. Clinic charts are reviewed for WHO stages and clinical data on health parameters and events. A study register is kept to record follow-up.

Attempts are made to obtain lab data from samples obtained at usual clinical care time points and thus are either collected at the same visit as the study questionnaires are administered or within two weeks if not the same day. The CD4 T cell counts are run on a FACScan (Becton Dickson) at a centralized site. Plasmas for HIV viral load testing (Roche Amplicor) are separated at the central laboratory for the Nairobi clinics, but separated and frozen at -20C and batched for transport from the rural district clinic. All plasmas are frozen at -80C at the central lab. Viral loads are run in batches using manufacturer controls.

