Time to virological failure	Improvement occurred	Virological failure after successful suppression	Kaplan-Meier survival analysis

Weight gain [lbs] and BMI	improvement occurred	Change in weight (lbs) and BMI [continuous]	T-test

Occurrence of opportunistic infections (OIs)	improvement occurred	Presence of AIDS defining opportunistic infection [binary]	Chi-squared test

Time to reporting of adverse drug events (ADEs)	improvement occurred	Presence of drug-related adverse event [time to event]	Kaplan-Meier survival analysis

Deaths (all cause)	improvement occurred	All-cause mortality [binary]	Chi-squared test and Kaplan-Meier survival analysis

SF-12	improvement occurred	Quality pf life questionnaire [continuous]	T-test

Satisfaction with care provided	improvement occurred	Questionnaire [continuous]	T-test

Level of disclosure of HIV status	improvement occurred	Disclosed to a family member [binary]	Chi-squared test

Impression of stigma	improvement occurred	Questionnaire [continuous]	T-test

Family dyamics	improvement occurred	Questionnaire [continuous]	T-test

Employment attendance	improvement occurred	Questionnaire [continuous]	T-test

Household member school attendance	improvement occurred	Questionnaire [continuous]	T-test

Cell phones lost/stolen	improvement occurred	Presence of cellphone [binary]	Poisson regression

Stopped taking HAART	improvement occurred	Self-report [binary]	Chi-squared test

Required active tracing for 12 month follow-up	improvement occurred	Field officers [binary]	Chi-squared test

3) **Subgroup Analyses:**			Regression methods with appropriate interaction term
Urban vs. rural	Distance affects adherence		
Female vs. male	Sex affects adherence		
Phone ownership (owned vs. shared)	Ownership affects adherence		
Level of education	Low education affects adherence		

4) **Sensitivity Analyses:**	improvement occurred	All outcomes	
a) Per protocol analysis			a) Chi-squared/T-test test
b) Adjusting for baseline covariates			b) Multivariable regression
c) clustering among individuals within a clinic			c) GEE

IMPORTANT REMARKS:

• The GEE[11] is a technique that allows to specify the correlation structure between patients within a hospital and this approach produces unbiased estimates under the assumption that missing observations will be missing at random. An amended approach of weighted GEE will be employed if missingness is found not to be at random.[12]

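### Time to reporting of adverse drug events is compared between arms although the intervention prompts reports weekly in the SMS arm only, and the direction that counts as improvement is not stated

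*Protocol article*

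**What the plan says.** Tables 1 and 3 of the protocol article name the outcome "Time to reporting of adverse drug events (ADEs"). Table 3 gives the measure as "Presence of drug-related adverse event [time to event"], the method as Kaplan-Meier, and the hypothesis as improvement, without a direction. The Secondary objectives section expects "fewer opportunistic infections, fewer adverse health events" in the SMS arm.

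The Intervention section states that each Monday the clinician "sends a text message (SMS) to all subjects in the intervention arm". Patients are to answer within 48 hours that they are well or that they have a problem. "The clinician then calls to follow-up and provide triage to any subjects that respond that there is a problem", and also calls those who do not answer within two days. The Control section says that controls are not sent these messages but may call the clinic on their own initiative.

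Under Data collection, the weekly log records the messages and responses, "including details related to phone access, medication adherence and health or illness issues as they arose". Control-arm calls go into a similar log. The same section provides a follow-up questionnaire at 6 and 12 months and a review of clinic charts, both for all participants. It does not say which of these sources supplies the adverse-drug-event date. The Ethics section confirms that only the analysis is blinded.

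**The concern.** The endpoint, as named, is the act of reporting. The intervention asks one arm every week whether there is a problem and telephones those who say yes or stay silent. The other arm is asked nothing between visits. A difference in time to reporting can therefore come from drug toxicity, from the prompting, or from both, and the Kaplan-Meier comparison cannot separate them.

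The missing direction makes this worse. Read against the objective of "fewer adverse health events", an earlier curve in the SMS arm is a bad result. Read as a measure of communication, the same curve is a good one. With only a generic statement of improvement, either significant result could be interpreted either way after the data are seen. If SMS truly reduced toxicity, prompted reporting could also mask the reduction.

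Blinded statisticians do not remove the problem, because it arises when events are ascertained. Adjustment for baseline covariates does not remove it either.

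**Working it through.** The documents give no figure for this outcome, so there is none to reproduce. The check has a textual part and an illustrative part.

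**Ascertainment by arm**

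| Route | SMS | Control |
|---|---|---|
| Weekly clinician enquiry | yes | no |
| Clinician call after a problem report or no reply | yes | no |
| Patient-initiated call, logged | yes | yes |
| Questionnaire at 6 and 12 months | yes | yes |
| Chart review | yes | yes |

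The first two routes exist in one arm only, and both bring reports forward. The last three are open to both arms.

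**Illustration 1: unequal reporting probability, equal true incidence**

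Inputs from the documents: 267 per arm (Sample size); two-sided alpha 0.05, with Bonferroni adjustment for secondary outcomes (Statistical methods). Table 3 lists 18 secondary outcomes, so the adjusted level is 0.05/18 = 0.0028, critical value 2.99. Assumed: 12-month incidence p of 20% to 40%; probability that an event is reported, s, as shown in the table.

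- Apparent HR = log(1 − p·s_SMS) / log(1 − p·s_control)
- Events d = 267·p·(s_SMS + s_control)
- Chance of a significant excess in the SMS arm = Φ(√(d/4)·log HR − critical value)

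Worked case, p = 0.30, reporting 60% (control) and 80% (SMS): HR = log(0.76)/log(0.82) = 1.38; d = 267 × 0.30 × 1.40 = 112; √(112/4) × log 1.38 = 1.72. At 0.05: Φ(1.72 − 1.96) = 40%. At 0.0028: Φ(1.72 − 2.99) = 10%.

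| Reporting, control vs SMS | HR, p = 20% to 40% | Chance at 0.05 | Chance at 0.0028 |
|---|---|---|---|
| 80% vs 90% | 1.14 to 1.16 | 9% to 16% | 1% to 2% |
| 60% vs 80% | 1.36 to 1.41 | 27% to 55% | 5% to 18% |
| 60% vs 90% | 1.55 to 1.63 | 50% to 87% | 15% to 53% |

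**Illustration 2: simulated delay and capture, equal true onset rate**

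Assumed: 30% or 50% incidence; 30% or 50% of SMS events reported at the next weekly text; all other reports at the next clinic contact, every 4 or 26 weeks, with 70% or 90% captured there. This gives 16 scenarios of 300 runs each. Apparent HRs were 1.05 to 1.48. The log-rank test rejected in about 3% to 77% of runs at 0.05 and in 0% to 39% at the Bonferroni level, where 15 of the 16 scenarios stayed at about 15% or less. The high end is one corner: 50% incidence, 26-week contact, 70% capture and 50% reporting by text.

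**Illustration 3: delay only**

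If every event is eventually reported and only the timing differs, a control interval of 26 weeks delays reports by about 13 weeks on average, with rejection of about 7% to 27% at 0.05. With a 4-week interval, rejection stays near 5%.

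**Check of a tempting remedy**

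One might drop from the comparison any event first learned through the SMS or call log. Under the assumptions of Illustration 2 this gave apparent HRs of 0.41 to 0.67 and rejection in 47% to 100% of runs at 0.05. It removes events mainly from the SMS arm, including events that the common sources would also have recorded, and so creates a larger bias in favour of SMS.

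**The case against.** The strongest reply is that the article does not say adverse-drug-event dates come from the phone log. Charts and the 6- and 12-month questionnaires cover both arms, and the logs have their own descriptive role under Nested studies. Taken only from the common sources, the bias would shrink. This stands as a limit: the effect is to be expected, not stated in the documents, and its size depends on a source that is not named. It does not dispose of the point. The outcome is named for reporting, no onset-based version is given, and a prompted call can lead to an earlier chart entry.

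A second reply is that quicker reporting may be intended, since the article describes an enhanced communication link and efficient sorting-out of adherence problems. It also does not equate adverse drug events with adverse health events. Both are fair. They support stating which construct is meant and which direction is improvement, because the present text permits either.

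Third, all rates in the illustrations are assumed, and Bonferroni keeps false rejection low in most scenarios. That also stands. The adjustment controls the test but leaves the hazard ratio and the curves biased.

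Two stronger readings are tempting. A reader might infer that the SMS arm is certain to show more events and that the result is therefore uninterpretable; with high capture and frequent contact in the control arm, the apparent HR is only about 1.05. A reader might also extend the point to opportunistic infections. That outcome is binary and limited to AIDS-defining infections, charts are reviewed in both arms, and no calculation supports the extension.

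**Conclusion.** The point holds for one secondary outcome. The endpoint as named mixes a direct effect of the intervention on reporting with drug toxicity, and the direction of improvement is undefined. If phone reports feed the endpoint, the bias as a measure of toxicity runs against SMS. An apparent HR of about 1.05 to 1.5 at equal true toxicity is a reasonable illustration, reaching 1.63 under the widest reporting gap tried. These figures rest wholly on assumed incidence, reporting probabilities and contact intervals. The primary analyses are not affected. The sponsor should make the change, but the trial's main conclusions do not depend on it.

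**What to change.** In Tables 1 and 3, define the between-arm comparison as occurrence of an adverse drug event by the 6- and 12-month visits, or onset date where it is recorded. Take it from the follow-up questionnaires and from chart entries at scheduled visits, in the same way in both arms. Count every event these common sources record, however it was first learned; do not exclude events because they first appeared in the SMS or call log. State that fewer or later events count as improvement. Report time to reporting from the logs separately, as a descriptive process measure alongside the log study already planned under Nested studies.

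The cost is mainly wording, since the questionnaires and chart review are already planned. It assumes that they capture adverse drug events; the article does not say whether onset dates are collected, and occurrence by visit avoids that need. Mild events between visits may be recalled less well, and weekly contact may still influence recall or chart entries in the SMS arm, so the bias is reduced and not fully removed.

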### Setting and participants

Subjects are recruited from three HIV comprehensive care clinics (CCC) in Kenya. One facility is an urban university-run clinic situated in a lower socioeconomic area of Nairobi, the second is an urban clinic attached to a faith-based hospital situated in a middle income area of Nairobi, and the third is a government-run clinic situated in a vast rural district of Kenya populated by pastoralists.

Patients are eligible to participate if they are initiating HAART for the first time (within two weeks before or after enrolment screening), if they are adults (at least 18 yrs old), if they owned or had sufficient access to a mobile phone (shared access is allowed if access is daily and the phone owner agrees to participate), and if they were able to sufficiently operate a cell phone to communicate using text-messaging (help by a partner is sufficient for illiterate subjects). Patients need to provide oral and written consent to participate. For patients who are illiterate, clear oral consent is obtained. Patients are excluded if they do not meet inclusion criteria or are not planning to attend the enrolment clinic for the planned study period (at least two years). Patients are considered newly initiating HAART if they have not taken HAART in at least one year and have not taken it ever for more than 2 months. Most prevention of mother to child transmission (PMTCT) regimens in Kenya include limited antiretroviral regimens and not true HAART, so participation in PMTCT is not an exclusion criteria. Therefore, the study covers a broad range of patients attending comprehensive care clinics (CCC) for ART in Kenya.

Participants are compensated for their participation time with money for lunch on study visit days (100 Kenya shillings). Patients are not provided cell phones or network airtime credit.

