#### Secondary outcomes

The potential benefits of the intervention are quite broad, so multiple secondary outcomes are of interest and were selected through academic collaboration. The secondary outcomes fall under the categories of health, quality of life, social factors, and economic indicators (see Table 1). The primary purpose of taking antiretroviral medications for HIV infection is to maintain or restore health in someone who is HIV infected. Several other factors that contribute to a subject's prosperity or overall well-being may be affected directly (by way of enhanced support mechanisms associated with the intervention), or indirectly (through improvements in health related to HAART effect). We therefore feel it is important to assess each of these outcomes independently.

**Table 1 T1:** Secondary Outcome Measures

**Secondary outcome measures (6 months and 12 months post initiation of HAART)**	**Type**
*Health outcomes*	
Self-reported adherence as a percentage	Binary
Suppressed HIV viral load (in copies)	Continuous
Immune reconstitution (change in CD4 T cell count from baseline)	
Time to virological failure	Continuous
Weight gain [lbs] and BMI	Time-to-event
Occurrence of opportunistic infections (OIs)	Continuous
Time to reporting of adverse drug events (ADEs)	Binary
Deaths (all cause)	Time-to-event
*Quality of life (QOL)*	Time-to-event
SF-12	
Satisfaction with care provided	Continuous
*Social factors*	Continuous
Level of disclosure of HIV status	
Impression of stigma	Binary
Family dyamics	Continuous
*Economic factors*	Continuous
Employment attendance	
Household member school attendance	Continuous
Cell phones lost/stolen	Continuous

HAART = highly active antiretroviral therapy, SF-12 = short form 12 adapted for regional application in Kiswahili.

In addition, we hypothesize that the intervention will lead to improved retention on ART.[5] Because participants are actively traced for twelve month follow-up visits, we will use composite retention outcomes. We define 'retained' as someone who followed-up on their scheduled visit without being traced and is still taking ART versus 'unretained' which includes subjects who stopped taking ART before their twelve month visit, who are lost to follow-up, or required active tracing after missing their scheduled twelve month appointment. We will report each element of the composite endpoints.[6]

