#### Sub-group analyses

Because a large clinical trial on this type of intervention has never been done before, we are interested in the interventions effect on various subgroups and the effect of multiple covariates on treatment outcomes. Subgroups of particular interests and potential covariates proposed are outlined in Table 2. Treatment arms will be compared with respect to potential covariates using continuous and categorical univariate analyses.

**Table 2 T2:** List of subgroups and potential covariates

**Subgroups of interest**	**Potential covariates**
Urban vs. rural	Age
By clinic	Gender
Female vs. male	Distance from clinic
Phone ownership (owned vs. shared)	Income level
Occupational designation	Cost to attend clinic
Level of education	Level of literacy
Usual mode of transportation used	Baseline quality of life
	HIV staging
	Level of disclosure of status
	Crossover into intervention

HAART = highly active antiretroviral therapy.

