#### Statistical methods

The intervention arm (SMS) will be compared against the control (SOC) for all primary analysis. We will use chi-squared test for binary outcomes, and T-test for continuous outcomes. For subgroup analyses, we will use regression methods with appropriate interaction terms (respective subgroup × treatment group). Multivariable analyses will be based on logistic regression (See Table 2) for binary outcomes and linear regression for continuous outcomes. We will examine the residual to assess model assumptions and goodness-of-fit. For timed endpoints such as mortality we will use the Kaplan-Meier survival analysis followed by multivariable Cox proportional hazards model for adjusting for baseline variables. We will calculate Relative Risk (RR) and RR Reductions (RRR) with corresponding 95% confidence intervals to compare dichotomous variables, and difference in means will be used for additional analysis of continuous variables. P-values will be reported to four decimal places with p-values less than 0.001 reported as p < 0.001. Up-to-date versions of SAS (Cary, NC) and SPSS (Chicago, IL) will be used to conduct analyses. For all tests, we will use 2-sided p-values with alpha = < 0.05 level of significance. We will use the Bonferroni method to appropriately adjust the overall level of significance for multiple primary outcomes, and secondary outcomes.

To assess the impact of potential clustering for patients cared by the same clinic, we will use generalized estimating equations [GEE] (ref) assuming an exchangeable correlation structure. Table 3 provides a summary of methods of analysis for each variable. Professional academic statisticians ([name]) blinded to study groups will conduct all analyses.

**Table 3 T3:** Variables, Measures and Methods of Analysis

**Variable/Outcome**	**Hypothesis**	**Outcome Measure**	**Methods of Analysis**
1) **Primary**	Intervention improved outcome from baseline to 6 months		
			
a) Adherence at 12 months		Percent adherence in previous 30 days >95% [binary]	Chi-squared test
			
b) Suppression of HIV viral load at 12 months		Viral load ≤400 copies/ml [binary]	Chi-squared test

2) **Secondary** Adherence percentage at 12 months	improvement occurred	Adherence % (>95%) [binary]	Chi-squared test

HIV viral load at 12 months	improvement occurred	Viral load (copies)	T-test

Immune reconstitution (change in CD4 T cell count from baseline)	improvement occurred	Cd4 T-cells/mm^3 ^(continuous)	T-test

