The multi-site randomized controlled trial design was specifically designed to incorporate a broad sampling of populations attending ART care clinics in Kenya. This approach risks diluting the statistical power to detect treatment responses which could be more easily seen in more homogenous patient groups. However, we feel there is a common thread of impact of cell phone usage across all populations in the region. This study design and analysis plan will allow us to evaluate several factors that may contribute a variable array of patient benefits. We are also aware that by consenting and participating in this study, both the healthcare providers and study subjects (including controls), are made more aware of the potential benefits of increased cell phone communications even outside the SMS protocol. This is known as the Hawthorne effect of participation in clinical trials, and may reduce the power to compare the effect of the SMS intervention against the true standard of care seen in non-study environments. Since it would be unethical to restrict communications between health care providers and patients, we have applied for ethics approval to compare adherence and other outcomes in this clinical trial with non-trial participants at the same or similar clinics. We recognize that blinding participants in a trial such as ours is impossible. However, our SMS texts are delivered in such a way as to a) reduce likelihood of disclosure to others around the patient and b) to act as a reminder of health, rather than HIV status, as our texts simply state 'how are you?'

All factors contributing to the success or failure of the intervention to improve health care management of patients are unlikely to have been predicted *a priori*. Therefore the results of this trial, including the qualitative nested studies and experiences of participating clinicians, will not only test the effectiveness of the described intervention protocol, but will instruct further development of the use of mobile telephony to improve health management in resource limited settings.

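### The HIV disclosure outcome takes no account of disclosure before enrolment, which dilutes any SMS effect and costs power without biasing the comparison

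*Protocol article*

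**What the plan says.** The Secondary objectives of the protocol article hypothesise that the SMS arm will show "improved social factors such as disclosure of their HIV status". Table 3 (Statistical methods) turns this into the measure "Disclosed to a family member [binary", tested by chi-squared. Table 1 sets the time points in its heading: "Secondary outcome measures (6 months and 12 months post initiation of HAART".

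The disclosure row is a status at follow-up. Two other secondary outcomes in the same table are written as changes: "Immune reconstitution (change in CD4 T cell count from baseline" and "Change in weight (lbs) and BMI [continuous".

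Baseline disclosure may enter elsewhere. Table 2 (Sub-group analyses) lists "Level of disclosure of status" among potential covariates, without saying that the baseline value is meant. Table 3, item 4b, plans multivariable adjustment for baseline covariates across all outcomes, as a sensitivity analysis.

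Two further statements bear on what disclosure means. Setting and participants admits patients without their own phone: "shared access is allowed if access is daily and the phone owner agrees to participate". The Discussion says the texts are delivered so as to "reduce likelihood of disclosure to others around the patient".

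**The concern.** Telling a relative about one's HIV status cannot be undone. A patient who had done so before randomisation is a certain yes at 6 and 12 months in both arms and carries no information about the intervention. The chi-squared test in all patients nevertheless includes everyone, so the more patients had already disclosed, the smaller the difference and the relative risk it can show.

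That share may not be small. Shared phones need the owner's agreement, and illiterate patients may be helped by a partner, so the entry rules could favour patients whose family already knows. This is an inference, because the article reports no baseline rate.

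At stake is a missed or understated effect on one of the social outcomes the trial sets out to test. A null result could mean that the SMS did nothing, or that few patients were left to change.

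A smaller point is that the row does not say whether only the participant's own decision to disclose counts. The Discussion treats exposure through the texts as something to reduce, but no row in Tables 1 or 3 records it.

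**Working it through.** The article gives no figure for disclosure, so there is none to reproduce. The calculation below is an illustration.

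**Inputs from the article:** 267 per arm as the enrolment target and 247 per arm before over-enrolment (Sample size); two-sided alpha 0.05, with Bonferroni for secondary outcomes (Statistical methods).

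**Assumed inputs:** new disclosure among patients undisclosed at entry, 55% SMS versus 35% control; share b already disclosed at entry, 50, 65 or 80%.

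**Proportions under the planned analysis.** In each arm, p = b + (1 − b) × new-disclosure rate. At b = 50%, control is 0.50 + 0.50 × 0.35 = 0.675 and SMS is 0.50 + 0.50 × 0.55 = 0.775. The difference is (1 − b) × 20 points = 10 points. The relative risk is 0.775/0.675 = 1.15, against 0.55/0.35 = 1.57 among the undisclosed.

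**Power.** Power = Φ[(d − 1.96 × SE0)/SE1], where SE0 = √(2p̄(1 − p̄)/n) and SE1 = √([p0(1 − p0) + p1(1 − p1)]/n).

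- All patients, b = 50%, n = 267: SE0 = 0.0386, SE1 = 0.0384, so Φ(0.63) = 0.74.
- Undisclosed at baseline only, n = 267 × 0.5 = 133.5, 0.35 versus 0.55: SE0 = 0.0609, SE1 = 0.0596, so Φ(1.35) = 0.91.

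| Already disclosed | Control vs SMS, all patients | Difference | Relative risk | Power, all (267/arm) | Power, undisclosed only | Same pair at 247/arm |
|---|---|---|---|---|---|---|
| 50% | 67.5% vs 77.5% | 10 points | 1.15 | 74% | 91% | 70% vs 89% |
| 65% | 77.25% vs 84.25% | 7 points | 1.09 | 54% | 79% | 51% vs 76% |
| 80% | 87% vs 91% | 4 points | 1.05 | 31% | 55% | 29% vs 52% |

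**Other assumed rates.** With new disclosure of 45% versus 30% and 247 per arm, power is 44% in all patients and 69% in the undisclosed at b = 50%, and 25% and 47% at b = 70%.

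**Bonferroni.** Table 3 has 18 secondary rows. If alpha is split over all of them (an assumption about how the correction is applied), 0.05/18 = 0.0028. With 267 per arm and 55% versus 35%, power is then about 34, 17 and 6% in all patients, against 62, 40 and 18% in the undisclosed.

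**Does the direction depend on the assumed rates?** Let r be the mean new-disclosure rate. Using d/SE0 for each analysis, the ratio (all patients to undisclosed only) is √(r/[b + (1 − b)r]), which is below 1 for any b above 0. With r = 0.45 and b = 50%, it is √(0.45/0.725) = 0.79. The loss follows from the definition, and only its size depends on the assumptions.

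**Is there bias?** If the new-disclosure rates are equal in the two arms, both have the same expected p for any b. Prior disclosures alone therefore create no apparent benefit.

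**The case against.** The strongest reply is that baseline adjustment is already foreseen. Disclosure level is a Table 2 covariate, item 4b covers all outcomes, and logistic regression is named for binary ones. If disclosure is irreversible, a model that includes baseline disclosure takes its treatment estimate from the undisclosed patients, which is close to the restriction proposed here. This is right as far as it goes. But the covariate is only a potential one, is not labelled as baseline, and belongs to a sensitivity analysis. The main test stays unadjusted.

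It can also be said that the trial is not powered for this outcome, that every disclosure rate above is assumed, and that an article condenses a fuller protocol and questionnaire. The first two points stand and limit the weight of this one. The third applies to the wording of the questionnaire item, but Table 3 itself fixes the measure and the test.

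Two stronger readings are tempting.

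- A reader might infer that the protocol contradicts itself, wanting disclosure in the Secondary objectives and avoiding it in the Discussion. It does not. The first concerns patients telling others, the second exposure to people nearby, and it is consistent to want more of one and less of the other.
- A reader might infer that a relative who finds out from a text is scored as a success for SMS. Nothing says so. Disclosed to a family member most plainly means the patient's own act. The hypothesis entry that improvement occurred stands against nearly every secondary outcome and is a between-arm hypothesis, not a rule for scoring patients. The texts ask only how the patient is. Voluntary disclosure prompted by the support is an effect the trial hopes to see.

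**Conclusion.** The point holds as a loss of sensitivity in one secondary outcome. As defined, the disclosure measure counts patients who could no longer change, and the main test ignores baseline. On the assumed rates, a 20-point effect shrinks to between 10 and 4 points, and power is 17 to 25 percentage points lower than in the analysis restricted to patients undisclosed at baseline (267 per arm, alpha 0.05). The direction holds for any non-zero share already disclosed, provided disclosure is irreversible. The size rests on rates that the article does not give. There is no bias towards either arm from prior disclosure, and the documents support neither a contradiction in direction nor the scoring of accidental exposure as success. What remains on that side is an ambiguity: the row does not say that only chosen disclosure counts, and unintended disclosure has no outcome row of its own. The weakness is minor, but worth correcting because the correction is cheap.

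**What to change.** Define the main analysis as new disclosure to a family member by 12 months among patients not disclosed to family at baseline. That group is fixed before randomisation, so the comparison stays randomised. Alternatively, keep all patients and adjust the main analysis for baseline disclosure. A test stratified by baseline disclosure is safer than a logistic covariate, which may not be estimable if every patient disclosed at baseline is still a yes at follow-up. Either way, label the Table 2 covariate as the baseline value.

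State that the outcome means disclosure by the participant's own choice. Report any unintended disclosure through study texts or calls separately by arm, and preferably by owned versus shared phone, which is already a subgroup of interest.

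The cost is one line in the outcome definition, confirmation that the baseline questionnaire records disclosure to family (its items are not shown), and one follow-up item on how the family member came to know. The restricted result applies only to patients undisclosed at entry, so the overall proportion disclosed in each arm should still be shown descriptively.
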